#### Open Up

Two open conversation skills relate to the objective to open up. First, *asking open questions* aims to encourage individuals to use open (as opposed to closed) questions to gain insights and understanding and to allow their conversation partner to discuss their story. Open-ended questions are 1 of the 4 core communication skills in motivational interviewing to help establish a mutually trusting and respectful relationship with a conversation partner [7,63] and a strategy to accommodate people’s basic psychological need for relatedness in Self-Determination Theory [66,85]. Asking open questions is also an important active listening skill to enhance understanding and build relationships [73], and this communication skill is cited in numerous health risk communication guides [79,81]. Second, to *be resilient if the other* (conversation partner) *is right* promotes respect for divergent views (respectful disagreement) to foster open mindedness, shared identity, and more positive conversational exchanges [58,59,72]. At the same time, being willing to acknowledge and accept when a conversation partner is right or makes a valid argument demonstrates humility and openness to opposing views [76].

#### Don’t Be Sad If It Doesn’t Work Out

The final objective involves preparing the individual for a case in which their conversation will not necessarily lead to a positive outcome or observable behavior change [79]. The open conversation skill is to *accept negative outcomes* without judgment or negative evaluation of the situation or the conversation partner. Acceptance, nonjudgment, and nonreactivity are important for emotion regulation and for reducing strong negative emotions in mindfulness and acceptance and commitment therapy [70,78,86,88]. Accepting that the conversation may be one of several and leaving open the opportunity for future conversations can keep communication channels open and maintain ongoing relationships [79].

### Intervention Delivery: Serious Game

We sought to deliver the intervention through a medium that had a strong evidence basis for promoting behavior change, was realistic and had strong ecological validity in terms of interpersonal communications during the COVID-19 pandemic, would motivate people to engage with the intervention, and could reach broad and diverse audiences. Gamified behavioral interventions have been found to promote positive behavior change across a variety of health-related areas, including asthma control, medication adherence, and diet [89], and were found to be more effective than inactive controls or nongamified interventions in improving physical activity behavior [90]. Games have also been used as educational tools across a variety of fields [91,92], such as teaching students role-playing and perspective taking to improve open conversation skills [22], and have been found to be effective at inoculating people against disinformation [93,94], specifically COVID-19 disinformation [95].

Serious games are games that do not have “entertainment, enjoyment or fun as their primary purpose” [21]. The learning benefits of serious games align with the goals of boosting interventions, in which the aim is to boost competences and in which motivation is key to intervention efficacy [49]. Serious games increase knowledge, build skills, and increase self-efficacy through design features within the game play that help players to select relevant information and integrate and organize the information with prior knowledge [96]. For instance, a first-person perspective can engage players in the learning experience, narrative and choice instill a sense of autonomy, interactions with game characters and personal reflection provoke empathy and relationship or community building, and mistakes and feedback processes can foster persistence [92,96]. Furthermore, serious games not only enhance motivation to learn but also have a strong motivational appeal [92,96].

Serious web-based games have the potential to reach a broad and diverse audience, can be accessed worldwide on mobile and desktop devices, and can be shared with others via web-based media. Edutainment mobile games aimed at educating remote or low-resource communities on issues such as agriculture and farming practices, health, livelihoods, and financial literacy have been disseminated in over 20 countries, with COVID-19–focused games reaching >2.7 million people across 11 countries in 2020 [97]. Furthermore, as social distancing and safety measures during COVID-19 have limited close interpersonal contact and people have increasingly turned to web-based communication to stay connected [98], mimicking widely used web-based communication applications (eg, using a messenger-type app) [99] has strong ecological validity [100]. Another goal of using this format was to facilitate adaptation, translation, and implementation into existing public health channels that may be fighting misinformation via chatbots (eg, WHO’s Health Alert Services [101-103]), including in low-resource settings [104]. Therefore, we designed a serious game based on a messenger app to build self-efficacy and open conversation skills by mimicking real-world conversations between vaccine advocates and their close contacts. Further details on the specific design features of the serious game and how the open conversations skills were implemented are provided in the *Methods* section.

### Overview of Intervention Hypotheses

In the previous sections, we have detailed the theoretical development of *The Good Talk!* intervention. Our next step is to conduct a research study to evaluate the efficacy of *The Good Talk!* serious game to improve people’s skills and competences to have open conversations about COVID-19 with vaccine-hesitant individuals. In the following sections, we present a detailed research protocol describing the planned evaluation study to be conducted along with the implementation of the game. Once completed, the results of the evaluation study will be reported in a separate publication.

The efficacy of the intervention game will be evaluated in a preregistered randomized controlled trial. Specifically, we aim to answer the following research question: “How well does *The Good Talk!* game improve people’s open conversation skills, perceptions of self-efficacy, and behavioral intentions to have open conversations with vaccine-hesitant individuals who are close contacts?” We will compare a group of participants who play the intervention game with a control group that will play the widely known noneducational game *Tetris*. *Tetris* was selected as the game for the control condition as it is in the public domain, and most people know how to play it without the need for practice or instruction. *Tetris* involves a similar amount of cognitive effort to play as the intervention game, it contains no content related to the study, and it has been used as a control game to validate other digital game-based learning interventions [62,94,105]. *Tetris* is an inactive control group (receiving no educational material), which is an appropriate design for assessing the absolute efficacy of the intervention [106].

Our primary hypothesis is as follows:

*Hypothesis 1: Relative to the control group, The Good Talk! game will result in a greater increase (boost) in participant’s skills to have an open conversation with a vaccine-hesitant individual*.

We also hypothesize the following:

*Hypothesis 2: Relative to the control group, The Good Talk! game will result in a greater increase in individual’s feelings of self-efficacy to have an open conversation with a vaccine-hesitant individual*.*Hypothesis 3: Relative to the control group, The Good Talk! game will result in a greater increase in intentions to have an open conversation with a vaccine-hesitant individual*.

## Methods

### Participants and Recruitment

Participants will be recruited to play the game via video or push notifications promoting *The Good Talk!* game on social media platforms (eg, WHO chatbot channels) and advertised via other WHO informational campaigns. Recruitment will be open to all interested individuals worldwide but will be limited to English language speakers. Participants will self-subscribe to the study by accessing the WHO game information web page via the public link or when shared by members in their social network. On the game information page, participants will be asked if, in addition to playing the game, they would like to participate in the research element (a similar approach was used to recruit participants to research elements in other serious web-based games [93,95]). Participants who are not interested in participating in the study will be sent directly to play *The Good Talk!* game; otherwise, they will be asked to opt-in to the study after giving informed consent. Participation in the research element of the game will be restricted to individuals aged ≥18 years. Participation in the study is voluntary, and no remuneration will be offered to complete the study.

Previous studies evaluating the effect of similar serious games on the development of competences report small-to-medium effect sizes averaging around f=0.18 [95,100,105]. A power calculation with a small effect size (f=0.18), power of 0.90, and α=.05 for an analysis of covariance on posttest open conversation skills suggests a total sample size of n=327. We will aim to collect 450 responses (225 per condition) to account for potential technical issues or possible poor-quality data. Data collection will continue until the prespecified sample size for each condition is reached. Preregistration of this study can be found on the Open Science Framework [107].

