### Objectives

The aim of this paper is to describe the theory behind the development of a new digital behavioral science intervention—*The Good Talk!*—designed to target vaccine-hesitant individuals through their close contacts (eg, family, friends, and colleagues) and to describe the methodology of a research study to evaluate its efficacy. *The Good Talk!* uses a serious game—a game that does not have “entertainment, enjoyment or fun as their primary purpose” [21]—to boost the competences of vaccine advocates to have open conversations regarding COVID-19 with their close contacts who are vaccine hesitant. Serious games have been used as educational tools to build skills, including teaching perspective taking to help students improve their open conversation skills [22] and inoculating people against misinformation (eg, the *Bad News* game [23]). Peer-led initiatives have been used to address mistrust in other domains, and communicating through relatable and trusted sources can lead to more acceptable and personal information exchanges, promoting prosocial behaviors when common identities are shared [1,19]. Furthermore, by focusing on boosting open conversation skills rather than addressing a specific cause of vaccine hesitancy, the approach has the potential to address a variety of reasons why an individual is vaccine hesitant [1,24] as well as build transferrable skills that can be applied across a variety of situations [25]. *The Good Talk!* is publicly available worldwide and will be evaluated in a preregistered randomized trial. Evaluating the impact of the intervention will be the subject of a future publication.

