### Design

Participants who enter the game website and agree to participate in the research study will be randomized to the experimental or control group (between subjects) and complete both a pre- and postgame survey (within subjects). The experimental group will play *The Good Talk!* game, and the control group will play the noneducational game *Tetris*.

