### Outcome Measures

#### Prior Experience With COVID-19 Vaccination

Participants will be asked whether they have had or are currently supportive of people getting the COVID-19 vaccination, whether they currently know someone who is hesitant toward getting the COVID-19 vaccination (and if so, their relationship with this individual), and whether they have previously tried to have a conversation about COVID-19 vaccination with a vaccine-hesitant individual.

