### Procedure

Participants will first answer the questions regarding their support for COVID-19 vaccination and their past experience speaking with vaccine-hesitant individuals. Participants will then complete a pretest survey containing the 8 open communication skills items and the self-efficacy and behavioral intention items. The experimental group will then play *The Good Talk!* game, which will take approximately 10 minutes to complete. The control group will play *Tetris* for a similar amount of time.

Following the game, participants will respond to a posttest survey containing the open communication skills, self-efficacy, and behavioral intention questions. Participants will also complete the implementation intention questions and a short demographic survey. At completion of the study, participants will be thanked for their time and invited to share the study with their friends. Participants in the control group will be given the option to play *The Good Talk!*. Figure 3 presents the flowchart of the study design and procedure.

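### Entry by public link to a game that is free on the same page, with no stated question or limit that identifies people who have already played or taken part

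*Protocol article*

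**What the plan says.** Participants and Recruitment in the protocol article sets the route in: "Participants will self-subscribe to the study by accessing the WHO game information web page via the public link or when shared by members". The same section says of people who decline the research: "Participants who are not interested in participating in the study will be sent directly to play" The Good Talk!. The Objectives section says the game "is publicly available worldwide and will be evaluated in a preregistered randomized trial".

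Two limits on entry are stated, both in Participants and Recruitment: "Participation in the research element of the game will be restricted to individuals aged ≥18 years", and "Recruitment will be open to all interested individuals worldwide but will be limited to English language speakers". The section Prior Experience With COVID-19 Vaccination lists the entry questions. They cover support for vaccination, knowing a hesitant person, and "whether they have previously tried to have a conversation about COVID-19 vaccination with a vaccine-hesitant individual". None concerns earlier play or earlier participation.

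Under Design, "Participants who enter the game website and agree to participate in the research study will be randomized to the experimental or control group". Under Procedure, controls may play The Good Talk! at the end, and finishers are "invited to share the study with their friends". The Results section gives one data-quality exclusion, on completion time, as a sensitivity check. Recruitment runs until each condition reaches its target.

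**The concern.** The intervention and the trial share one front door. Someone can decline the research, play the game, and later return and opt in. A control can finish, play the game, and come back. The entry data as listed would not distinguish either person from a newcomer.

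Two things are at stake. The first is dilution: a previously exposed participant has had some or all of the training before the pretest, so the contrast between the games shrinks for that person whichever arm they join. The second is repeat entry. If one person contributes more than one record, the records are not independent, the same person may sit in both arms, and anyone who had completed the study has already met both fixed sets of skill items, which undercuts the purpose of using different sets before and after play. Neither can be put right afterwards if the information is not collected at entry.

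**Working it through.** **Reproducing the plan's figure.** Inputs from Participants and Recruitment: f = 0.18, power 0.90, α = 0.05, analysis of covariance, total 327, target 450 (225 per condition). For two equal groups, d = 2f = 0.36. Power comes from the noncentral F distribution with df1 = 1, df2 = N − 3 (two groups, one covariate) and noncentrality λ = N·f².

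- N = 327: λ = 327 × 0.0324 = 10.59, power 0.901. N = 327 is the smallest total that reaches 0.90, so the stated figure reproduces.
- N = 450: λ = 450 × 0.0324 = 14.58, power 0.968.

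The sample size itself is sound.

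**Dilution.** The exposed share c is not in the article; 5% to 30% is an assumed range. Assume also that exposed participants gain nothing further in either arm and that the outcome SD is unchanged. The contrast is d among newcomers and zero among the exposed, so the average is d(1 − c), and f becomes 0.18(1 − c).

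| c | f | d | Power, N = 450 | N for 90% power |
|---|---|---|---|---|
| 0% | 0.180 | 0.360 | 0.968 | 327 |
| 5% | 0.171 | 0.342 | 0.952 | 362 |
| 10% | 0.162 | 0.324 | 0.929 | 403 |
| 20% | 0.144 | 0.288 | 0.862 | 509 |
| 30% | 0.126 | 0.252 | 0.760 | 664 |

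Power at 450 stays at or above 0.90 until c is about 15%.

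**Exclusion instead of dilution.** If exposed and repeat entries can be recognised and removed, 450 − 327 = 123 entries (123/450 = 27%) can go before the total falls below 327.

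**Repeat entry.** No arithmetic applies; the text has to be read across sections.

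- Entry and consent trigger randomisation (Design). No section says whether a returning visitor keeps the first allocation.
- The Table 2 footnote fixes which items are in the pretest, and the rest form the posttest. A person who completed the study once has seen both sets. A person who left during the game has seen only the pretest set, because the posttest follows play (Procedure).
- Partly completed surveys are analysed where possible (Results), so two records from one person could both enter the analysis.
- The planned counts of dropouts and of partial and complete surveys per condition (Strengths and Limitations) do not link records. A person who left one condition and completed the other would appear as a dropout in the first and a completer in the second.

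**The case against.** A reader might infer that someone allocated Tetris can reload the page until given The Good Talk!. The article does not support that. It never says that a reload produces a new allocation, and a device or cookie check is the kind of platform detail a journal article may leave out; the preregistration and the flow diagram are not available here. The motive is also weak. Anyone who wants the game can decline the research and have it at once, controls are offered it afterwards and are told so, no payment is made, and a second attempt would mean consenting and taking the pretest again. This objection stands, so repeat entry is a possibility to close off, not a documented flaw.

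A reader might also infer that earlier players bias the comparison between arms. Those who enter once are randomised like everyone else and should split evenly, so they cause dilution, not imbalance. The pretest covariate can absorb some of the extra spread between exposed and new participants, though it does not restore the lost contrast.

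It is fair to add that the Abstract describes the game as still in development, so no pool of earlier players is shown to exist at launch, and that a friend who arrives by a shared study link may be new to the game. The assumption of no further gain is deliberately severe.

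Strengths and Limitations does concede self-selection to condition and answers it with reassurance and dropout counts. Those measures lower the motive to re-enter, but they cannot detect earlier play or a second entry.

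What remains is that the article does set out its eligibility limits, its entry questions and its quality check, and none of them identifies prior exposure.

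**Conclusion.** The point holds as a gap in what is captured at entry. As described, the plan would enrol people who have already played or taken part without recognising them, and the analysis could not separate them later.

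For single entrants the consequence is a smaller estimated effect and some loss of power. It is modest at low exposure (0.93 at 10%) and material at higher exposure (0.86 at 20%, 0.76 at 30%), with the 0.90 level lost at about 15%. These figures rest on an assumed exposed share, no further gain among the exposed and an unchanged SD; the true share is unknown.

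For repeat entry no size can be given. If it occurs it affects independence and the integrity of allocation, which a larger sample does not repair, but the article does not show that it would occur. The stated sample size is correct and is not in question. This is an inexpensive improvement to make before recruitment opens.

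**What to change.** Add one question before randomisation asking whether the person has already played The Good Talk! or taken part in this study. Either send those who answer yes to the game without enrolling them, or enrol and flag them and exclude them from the primary analysis; state which in advance. State also that only each person's first entry counts, analysed under the first allocation. If the platform does not already keep the allocation for a returning visitor, set a browser token that does. If it does, one sentence saying so settles the repeat-entry part.

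The cost is one survey item and at most one platform setting. There are downsides. The question relies on honest recall. A token will turn away a few people who share a device. Under the first-entry rule, people who left during their first game contribute an entry without a posttest. Some entries will be excluded, but the margin of 123 between 450 and 327 leaves room for that.

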### The Good Talk! Game

The intervention game was developed in collaboration with the game design company “Tiltstudio,” that has experience designing serious games including “Bad News,” “Go Viral,” and “Harmony Square,” targeting misinformation, COVID-19 misinformation, and political misinformation tactics, respectively. The game was designed to simulate messenger-type conversations between participants and close contacts in their social network. Messenger-type technologies are dyadic, informationally rich, synchronous, and mimic interpersonal communication and are therefore better suited for establishing a sense of connection and generating empathy [19]. At the same time, they represent a realistic communication platform familiar to many users worldwide [99], which increases the ecological validity of the intervention [100]. The game design implements instructional techniques found in a meta-analysis to be effective at improving learning and motivation in serious games, such as feedback (providing feedback or guidance on whether an answer is correct), reflection (participants are asked to reflect on their responses), level of realism (the game uses basic and cartoon-like representations), and narrative elements [96,108].

The game consists of 5 chapters in which the participants have conversations with characters representing their close contacts. In the first chapter, participants are introduced to the objective of the game, that is, to have as many people attend an event that they are organizing and to earn points for the good talk skills. The participant is asked to select an avatar to represent themselves and can choose between 1 of 4 social events they would like to organize (eg, birthday party, dinner, dance party, or housewarming).

The remaining 4 chapters see the participants encounter characters within their close ties who are motivated by reactance (negative affective reaction when one feels personal freedoms are being threatened), skepticism (doubting knowledge or claims), and inertia (opposing change or action) when discussing COVID-19 measures for the social event. As the conversation develops, the player must select from ≥2 conversational responses that affect the participant’s pathway toward the game objective and the points they earn on a Good Talk Meter. The Good Talk Meter increases with response choices that represent good open conversation skills and decreases for those that represent bad open conversation skills. In each chapter, participants are guided by a *Good Talk Guide* who offers advice and reinforces or educates participants about the strategies based on their selections. A brief description of the objective of each chapter is provided in Table 1, and a screenshot of the game interface is shown in Figure 2.

**Table 1 table1:** Brief overview of the goal and open conversation skills for each chapter.

Chapter	Goal
Introduction	The participant is introduced to the objective of the game and asked to select an avatar and an event they would like to plan. An overview of *The Good Talk!* skills is provided to participants along with the definition of what it means to have an open conversation.
Gain trust	The participant converses with someone who is worried about their kids not being vaccinated and whose kids are skeptical about the government’s use of COVID-19 antigen tests. The participant is encouraged to gain the trust of the conversation partner and, in turn, to encourage their partner to use open conversation skills to gain the trust of their children by expressing their concerns, finding mutual value, and supporting their kid’s autonomy.
Offer support	In this chapter, the conversation partner mistrusts the seriousness of the pandemic, is skeptical about the evidence, and does not see a personal need to get vaccinated. The participant is encouraged to ask for the perspective of their conversation partner rather than argue, with the goal to understand their views and to continue the conversation. By acknowledging their partner’s perspective and concerns, the participant is encouraged to find some common ground so that both feel comfortable attending the event.
Open up	The conversation partner is vaccinated but does not see a need to get the booster vaccination after reading some misinformation on the web and is reluctant to change their mind. The partner is overwhelmed by information and the impact of restrictions. By asking open questions, not being dismissive of their partner’s feelings or concerns, and accepting their points while being respectful of divergent views, the goal is to help the partner overcome their inertia.
Don’t be sad if it doesn’t work out	In the final chapter, the participant encounters a conversation partner who is against vaccination, who mistrusts the government, and who continues to share fake news and misinformation rather than engage in an open conversation. Rather than argue, the participant is guided to not react negatively and to accept that the conversation will be unlikely to lead to a positive outcome.

